##### Provision for post-trial care {30}

Post-trial care is provided as part of the clinical standard protocols. The intervention ends by discontinuing the arterial line for invasive blood pressure monitoring and extubation, respectively. From that time on, the only study-specific intervention will be the 3-month follow-up visit and questionnaire, for which the patients are invited at the time of hospital discharge.

### Outcomes {12}

#### Primary endpoint

Death from any cause orDischarge from hospital in a state of Cerebral Performance category 3 or 4, whichever occurs first

#### Secondary objective

Analysis will compare the two target blood pressure groups with respect to:
Time to
Initiation of renal replacement therapy orDeathNeuron-specific enolase (NSE) level at 48 hMOCA score at 3 months (lowest score allocated to patients not available for follow-up, including deceased patients)Modified Ranking Scale (mRS) and CPC at 3 monthsNT-pro-BNP at 3 months (highest value allocated to patients not available for follow-up)eGFR and LVEF at last available measurement within 3 months of follow-upDaily cumulated vasopressor requirement during ICU stay and need for combination of vasopressors and inotropic agents or mechanical circulatory support

##### Safety

The OHCA population admitted to intensive care is a critically ill group of patients. Most adverse events may be of a potentially serious nature but are often common in this patient group. Cardiac arrest patients and patients being unconscious for any other reason are at great risk of developing adverse events. Adverse events will be recorded daily according to 7.1. With regard to the trial intervention, relevant SAEs are considered to be death, need for mechanical hemodynamic support, and need for renal replacement therapy in the first 3 days.

##### Safety variables-adverse events (AE)

Major bleeding: Uncontrolled bleeding (> 1 unit of blood/10 kg/1 h), bleeding causing fatality; symptomatic bleeding in critical organ, e.g., intracranial, intraspinal, intraocular, intraarticular, pericardial; other bleeding, e.g., retroperitoneal, muscular, solid organ, thoracic with Hb ↓ > 50 g/L (5 g/dl; 3.1 mmol/L) and requiring > 2 units of transfused blood

Infection: Severe sepsis^1^, septic shock^2^, pneumonia during or after ventilator therapy, others

Renal impairment: Need for continuous renal replacement therapy (CRRT) or intermittent hemodialysis (IHD)

Electrolyte disorders: Hypokalemia (< 3.0 mmol/l), hypophosphatemia (< 0.7 mmol/l), hypomagnesaemia (< 0.7 mmol/l)

Metabolic disorders: Sustained hyperglycemia (> 10 mmol/l > 4 h), hypoglycemia (< 3.0 mmol/l)

Arrhythmia: VF, VT, tachycardia > 130/min, bradycardia < 40/min, atrial flutter, atrial fibrillation, need for pacing, circulatory collapse mandating CPR

Seizures: Tonic-clonic, myoclonic, electrographic status epilepticus

### Participant timeline {13}

Safety variables and adverse events will be recorded continuously during the first 7 days, when the patient is in the intensive care unit. Adverse event occurring later than this will be evaluated at the scheduled follow-up visit at 90 days. Hereafter, no follow-up is planned.

See SPIRIT Table 1 and sections describing primary and secondary outcomes.

**Table 1 Tab1:** Schematic presentation of the study time line

	Study period										
Enrollment	Pre-allocation	Post-allocation									Follow-up
Timepoint	ROSC to randomization	0 h	6 h	12 h	24 h	36 h	48 h	72 h1	96 h1	120 h1	Days 30 and 90
**Enrollment**											
**Eligibility screen**	x										
**Informed consent**		Legal guardian and next of kin									Patient as soon as possible
**Randomization**	x										
**Interventions**											
**Target blood pressure**		x					Until invasive BP monitoring is discontinued				
**Oxygenation**		x					Until extubation				
**Active post-TTM fever management**		x				TTM device discontinued after 36 or 72 h					
**Assessments**											
**Biochemestry2**		x			x		x	x	x	x	
**Troponin T and CKMB**		x	x	x	x	x	x	x			
**Biobank samples**		x			x		x				
**ECG**		x	x	x	x	x	x	x	x	x	
**Swan-Ganz-based measurements**		x	x	x	x	x	x	x			
**Automated pupillometry**		x	x	x	x	x	x	x	x	x	
**ABG and VBG**		x	x	x	x	x	x	x			
**Creatinine clearance**							x		x		
**CPC and mRS score**											x
**MOCA score**											Only day 90

*ROSC* return of spontaneous circulation, *TTM* Targeted Temperature Management, *ECG* electrocardiogram, *ABG* arterial blood gas, *VBG* venous blood gas, *SOFA score* Sequential Organ Failure Assessment, *CPC* Cerebral Performance Category, *mRS* modified Rankin Score, *MOCA* Montreal Cognitive Assessment

1: Assements made if patient is still admitted to the ICU

### Sample size {14}

Sample size estimation is based on blinded BP target allocation and on the assumption that no interaction with the oxygen intervention exists.

The combined primary outcome is time to death or hospital discharge in a state of CPC 3 or 4. We are planning a study with 400 experimental subjects, 400 control subjects, an accrual interval of 48 months, and additional follow-up after the accrual interval of 3 months. Prior data indicate the 6-month mortality is 33% overall. Assuming a mortality of 28% in the superior group compared to 38% in the inferior groups, we will need to include 732 patients in total or 846 patients in total to achieve a power of 0.8 and 0.9, respectively. The type I error probability associated with this test of the null hypothesis that the experimental and control survival curves are equal is 0.05.

Loss of final measurement is expected, but from the experience from the previous trial, the number of missing follow-up assessments is small (< 5%) and will not result in an increase of the number of patients needed.

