### Trial design {8}

Multicenter, randomized trial in 2*2 factorial design allocating comatose OHCA patients to one of two target blood pressures (double blind) and restrictive vs. liberal oxygenation (open label) during ICU stay with blinded outcome evaluation. Both interventions allocate patients in a 1:1 ratio. The design is a superiority trial.

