### Interventions

#### Explanation for the choice of comparators {6b}

As both main interventions (arterial blood pressure and oxygenation targets) are compliant with the current guideline for post-cardiac arrest management, there is no formal hypothesis suggesting the superiority of either intervention. Two-sided tests were applied in the sample size estimation.

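### The stated totals of 732 (power 0.8) and 846 (power 0.9) are inconsistent: 846 gives about 0.86 to 0.88, and 0.9 needs about 905 to 966

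*Protocol article*

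**What the plan says.** All of this stands in the protocol article.

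- **Planned size** (Sample size {14}): "We are planning a study with 400 experimental subjects, 400 control subjects, an accrual interval of 48 months", with "additional follow-up after the accrual interval of 3 months".
- **Event rates** (same section): "Prior data indicate the 6-month mortality is 33% overall". The effect is then set by "Assuming a mortality of 28% in the superior group compared to 38% in the inferior groups".
- **Totals and power** (same section): "we will need to include 732 patients in total or 846 patients in total to achieve a power of 0.8 and 0.9, respectively".
- **Type I error** (same section): the error probability for "the null hypothesis that the experimental and control survival curves are equal is 0.05".
- **Sidedness** (Explanation for the choice of comparators {6b}): "Two-sided tests were applied in the sample size estimation".
- **Allocation** (Trial design {8}): "Both interventions allocate patients in a 1:1 ratio".

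The sample size section assumes no interaction between the two interventions and adds no patients for missing follow-up, which it expects to be under 5%. It does not name the formula used.

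**The concern.** With the effect and the type I error fixed, raising power from 0.8 to 0.9 increases the required sample by about a third. The stated totals rise by only 16% (846/732 = 1.156). At least one of them must therefore carry the wrong power. The planned 800 lies between the two, and the article gives no other power figure, so a reader who wants the power of this trial will use these totals as the reference points.

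**Working it through.** **Inputs.** p1 = 0.28, p2 = 0.38, difference d = 0.10, mean 0.33; two-sided alpha 0.05 (z = 1.960); z = 0.8416 for power 0.8 and 1.2816 for power 0.9; equal arms; no inflation.

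**Step 1: reproduce 732.** The per-arm size without continuity correction is

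n = [1.960·√(2·0.33·0.67) + z_power·√(0.28·0.72 + 0.38·0.62)]² / d²

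The square roots are 0.6650 and 0.6612.

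- Power 0.8: (1.3033 + 0.5565)² / 0.01 = 345.9 per arm, total 692.
- Power 0.9: (1.3033 + 0.8474)² / 0.01 = 462.6 per arm, total 926.

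The continuity correction is n_c = (n/4)·[1 + √(1 + 4/(n·d))]².

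- Power 0.8: 365.6, rounded up to 366 per arm, **total 732**. This is the article's figure.
- Power 0.9: 482.4, rounded up to 483 per arm, **total 966**, against the stated 846.

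**Step 2: log-rank check.** The article describes a test of survival curves. Under proportional hazards the hazard ratio is ln 0.72 / ln 0.62 = 0.687, and its logarithm is −0.3751. Schoenfeld events = 4·(1.960 + z_power)² / 0.3751².

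- Power 0.8: 223.1 events; at 33% events, about 676 patients.
- Power 0.9: 298.7 events; about 905 patients.

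Rounding events up first gives 679 and 906. Freedman's formula gives about 694 and 927.

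**Step 3: power at the stated and planned totals.** For the corrected test, the per-arm size m is first reduced to m − 2/d + 1/(m·d²): 423 becomes 403.2 and 400 becomes 380.25. The uncorrected formula is then solved for power.

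| Total | Corrected | Uncorrected | Log-rank (Schoenfeld) |
|---|---|---|---|
| 732 | 0.800 | 0.822 | 0.830 |
| 800 | 0.836 | 0.854 | 0.862 |
| 846 | 0.857 | 0.873 | 0.880 |

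The shortfall of 846 against the total for power 0.9 is 966 − 846 = 120, 926 − 846 = 80, or 905 − 846 = 59.

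**Step 4: a check that depends little on the formula.** The ratio of sample sizes should be (1.960 + 1.2816)² / (1.960 + 0.8416)² = 1.339, or 966/732 = 1.32 with the correction. The stated pair gives 1.156. A smaller alpha does not explain it: the ratio is still 1.27 at alpha 0.01 and 1.22 at 0.001.

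**Step 5: other routes to the pair.** Totals for power 0.8 and 0.9:

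- One-sided: 546 and 754, or 586 and 794 with correction.
- Uncorrected, inflated for 5% dropout: 729 and 975.
- Hazard ratio taken as 28/38: above 1,000 for both.
- Exponential survival with 48 months of accrual and 3 of follow-up: about 299 and 399.

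Unpooled variance, the arcsine method and 10% dropout inflation were also tried. None of these gives 846 at power 0.9. The corrected formula needs 832 for power 0.85, so 846 is close to a figure for 0.85.

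**The case against.** The strongest reply is that nothing in the trial depends on 846. The article plans 400 + 400 and offers 846 only as a benchmark. The planned 800 exceeds the total for power 0.8 under each of the three calculations in the table (676 to 732). Linear interpolation between the stated totals puts 800 at 0.80 + 0.10·(68/114) = 0.86. That agrees with the log-rank figure of 0.862, the closest match to the planned proportional hazards analysis, and is at most about 2.4 points above the corrected figure of 0.836. All of this stands, and it limits the point to a reporting correction.

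Several stronger readings are tempting, and the document does not support them.

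- **That the trial claims power 0.9 and lacks it, or is underpowered.** It makes no such claim for its 800 patients, and 800 clears 0.8 under the assumed rates.
- **That a neutral result would be over-read.** An error of at most 2.4 points would not change how such a result is interpreted.
- **That not stating the power of 800 is itself an error.** The article condenses a fuller protocol, and leaving a figure out is not a mistake. The figure is proposed only as the natural replacement for the wrong one.
- **That using mortality for a composite endpoint defeats the calculation.** The rates are mortality rates, whereas the primary endpoint also counts discharge in CPC 3 or 4. The article gives no composite rate. If the overall composite rate were 38% to 48% (an assumption) with the same 10-point difference, log-rank power at 800 would be about 0.84 to 0.82, still above 0.8.
- **That the 6-month horizon or the accrual inputs are further errors.** The accrual model reproduces neither total, which shows only that the formula is not named. No numerical failure has been shown from the 6-month rate.

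**Conclusion.** The point holds as a narrow numerical correction. For 28% versus 38% at two-sided 0.05, with equal arms and no inflation, 732 is right for power 0.8 by the continuity-corrected formula and 846 is wrong for 0.9. The total needed is 966 by that formula, 926 without correction and about 905 by log-rank; 846 gives 0.857 to 0.880, which is 2 to 4 points below its label. The log-rank figures assume proportional hazards and 33% events overall. How 846 arose cannot be told from the document; the finding that no formula yields it covers only those tried, but the ratio argument does not rest on that list. The adequacy of the planned 800 is not in question: its power is about 0.84 to 0.86 under the assumed rates. The consequence is modest.

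**What to change.** In Sample size {14}, either delete 846 as the figure for power 0.9 or replace it with the correct total and name the formula: 966 (continuity-corrected two proportions, the method that yields 732), 926 (uncorrected) or about 905 (Schoenfeld log-rank). Add that the planned 800 patients give a power of about 0.84 to 0.86 for 28% versus 38%, and that these are mortality rates and not rates of the composite primary endpoint.

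The cost is one or two sentences. The article reports that the last patient has been included, and neither enrolment nor any analysis changes.

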### Recruitment {15}

Patients are included in the trial when arriving at the tertiary center and if all inclusion criteria and no exclusion criteria are present. The formal inclusion and randomization are performed by the attending physician via a dedicated website.

### Assignment of interventions: allocation

#### Sequence generation {16a}

The allocation of treatment goals has been performed in a 1:1:1:1 manner, using varying block sizes of 4–16.

The randomization to duration of device-based active temperature intervention (substudy) has been performed independently.

#### Concealment mechanism {16b}

Inclusion and randomization are performed via a dedicated website, and the allocation is kept concealed until the time of randomization (oxygenation target and duration of device-based post-TTM temperature management). The blood pressure intervention is concealed as the blood pressure module is labeled by a unique ID number, which is the patient’s study ID. The blood pressure module has been adjusted as described above before the inclusion of the patient.

#### Implementation {16c}

The attending physicians will have access to the trial inclusion webpage and assess eligibility criteria and inclusion of patients in the trial. The webpage will automatically request consent from the assigned.

### Assignment of interventions: blinding

#### Who will be blinded {17a}

Staff and study personnel will remain blinded to the allocated blood pressure target, as information of the blood pressure allocation is available to the core lab, adjusting the blood pressure modules and the person able to perform unblinding if deemed necessary by the treating physician.

#### Procedure for unblinding if needed {17b}

A person will be available for unblinding if necessary. However, as unblinding should only occur for safety reasons, and the blood pressure module may be switched to a clinical non-manipulated device with minimal delay, we expect a limited need for unblinding.

### Data collection and management

#### Plans for assessment and collection of outcome {18a}

Individual patient data will be handled as ordinary chart records and will be kept according to the legislation (e.g., data protection agencies) of the Danish health system. The study uses electronic data collection only, besides the consent forms that are on paper. The study database will be maintained for 15 years and anonymized if requested by the relevant authorities.

Danish legislation regarding the respect for patients’ physical and mental integrity and rights will be respected. Approval for storing data relevant to the trial, including potentially sensitive information, will be sought from the relevant authorities.

#### Plans to promote participant retention and complete follow-up {18b}

Staff dedicated to the ensure participant retention and promote adherence to the planned follow-up visit has been allocated to both sites involved in the trial. When participants are unable to attend an in-hospital follow-up visit, we offer a visit in the patients’ home, a telephone-based assessment of the neurological outcome, and mailing the questionnaires to the patient, in that order. Patients and relatives are not offered financial support for visiting, but expenses for transportation may be covered in selected cases.

Patients who discontinue or deviate from the intervention protocols will remain in the study database, if a consent for the data handling can be obtained, in which case a full data entry will be provided.

#### Data management {19}

Data is stored in a RedCAP® database hosted by the Regional IT department. Data is entered by dedicated study personnel and data quality is monitored. Data quality is monitored by the primary investigator by random sampling. A GCP monitor will review and validate consent forms, eligibility criteria for the trial, and endpoint data.

#### Confidentiality {27}

Confidentiality is ensured by the database system (RedCAP® and that medical data and patient’s sensitive data is accessed by trained medical staff only with valid authorization with the Danish Health Care Authorities). Anonymized data for meta-analyses may be provided after the publication of the main manuscripts.

#### Plans for collection, laboratory evaluation, and storage of biological specimens for genetic or molecular analysis in this trial/future trials {33}

The database may be supplemented by other clinical information and by novel analyses of the biobank material. The ethics committee will be consulted if there is uncertainty of the planned analyses or data catchment is covered by the informed consent

### Statistical methods

#### Statistical methods for primary and secondary outcomes {20a}

The primary outcome (death or severe neurological injury at time of hospital discharge CPC 3–4) for the blood pressure and oxygenation interventions will be analyzed and reported separately in a proportional hazard model (proc phreg) as a crude analysis with no co-factor adjustments. The number and fraction of the population with the endpoint will be reported.

No interaction of the two interventions is expected, and the interaction of the two will be analyzed and reported with the blood pressure target intervention. A Kaplan-Meier estimate plot will be presented with a maximum of 180 days.

Baseline and demographic data will be presented in a table, but no formal statistical testing will be performed due to the randomized design of the trial. A figure presenting the mean blood pressure or PaO_2_ respectively ±1.96SD (representing 95% of the observed cases) will be presented.

For the secondary outcomes, the time to renal replacement therapy and time to death will be compared in the proportional hazard model. NSE, MOCA score, Modified Rankin scale and Cerebral performance score, NT-pro-BNP, eGFR, and LVEF (at 3 months or last known value) and daily cumulated vasopressor requirement during the ICU stay will be reported and compared by a *t* test, and logarithmic transformation will be applied if data is skewed.

Safety variables: Major bleeding, infection, renal impairment (need for dialysis), electrolyte or metabolic disorders, arrhythmia, and occurrence of seizures and or shivering will be reported and compared by the chi-square test.

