### Objectives {7}

### Primary objective

To evaluate the superiority of one of the two blood pressure targets investigated: approximately 63 mmHg and approximately 77 mmHg and, separately, superiority of on the two PaO_2_ targets (restrictive vs. liberal oxygenation) with regard to a combined endpoint of time to:
Death from any cause orDischarge from hospital in a state of Cerebral Performance category 3 or 4, whichever occurs first

The hospital stay includes tertiary center as well as the local hospital and or specialized hospital-based neurological rehabilitation.

A stratified analysis by the following predefined design variables will also be performed: sex, age above median, pre-arrest renal failure GFR (< 30 ml/min or current renal replacement therapy), pre-arrest hypertension, pre-arrest chronic obstructive pulmonary disease, shockable primary rhythm, and suspected STEMI on initial ECG.

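### The primary Cox model is valid but expressly unadjusted; a few baseline covariates already recorded, notably age and shockable rhythm, would probably add power at little cost

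*Protocol article*

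**What the plan says.** Under Statistical methods for primary and secondary outcomes {20a}, the two interventions are analysed separately in a proportional hazards model, "as a crude analysis with no co-factor adjustments". The other randomised factor enters only through an interaction analysis, reported with the blood pressure results.

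The Primary objective adds: "A stratified analysis by the following predefined design variables will also be performed". Its list covers sex, age split at the median, pre-arrest renal failure, hypertension, COPD, "shockable primary rhythm" and suspected STEMI. Methods for additional analyses {20b} repeats the list for a forest plot and adds site. Neither section changes the primary test.

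Sequence generation {16a} describes 1:1:1:1 allocation "using varying block sizes of 4–16" and names no stratification factor, though an article may condense this.

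**The concern.** The article does not leave adjustment open for the analysis plan: it rules adjustment out of the primary model. Yet it names variables that can be expected to carry prognostic information, and they will be in the database whichever model is used. In a Cox model, leaving out a baseline variable that predicts the outcome lowers the power of the treatment comparison.

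At stake is efficiency in a trial with little power to spare. Sample size {14} cites targets of 0.8 and 0.9, and the planned 800 patients fall between them.

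**Working it through.** **Inputs**
- Type I error: the null hypothesis "that the experimental and control survival curves are equal is 0.05" (Sample size {14}). Sidedness: "Two-sided tests were applied in the sample size estimation" (section {6b}).
- Effect: "Assuming a mortality of 28% in the superior group compared to 38% in the inferior groups" (Sample size {14}). These are mortality figures; I use them for the composite, as the article does.
- Size: 400 + 400 = 800 (Sample size {14}).
- Covariate strength and prevalence: not given in the document. All values below are assumptions.

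**Step 1. Reproduce the article's figure (power 0.8).** Mean risk is 0.33.
- Uncorrected n per arm = [1.960·√(2·0.33·0.67) + 0.842·√(0.28·0.72 + 0.38·0.62)]² / 0.10² = (1.303 + 0.556)² / 0.01 ≈ 346, so 692 in total.
- With continuity correction: n′ = (n/4)·[1 + √(1 + 4/(n·0.10))]² ≈ 366, so 732 in total. This matches the article exactly, so its basis is an unadjusted comparison of two proportions.
- The 846 quoted for power 0.9 does not reproduce by the same formula, which gives 966; 846 patients give about 86%. That is a separate matter and is noted only because it shows how little margin there is.

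**Step 2. Crude power at 800.**
- Two proportions: (0.10 − 1.960·√(0.4422/400)) / √(0.4372/400) = 0.0348/0.0331 = 1.054, power 85.4%.
- With continuity correction (0.10 replaced by 0.0975): 0.978, power 83.6%.
- Cox (Schoenfeld): HR = ln 0.72 / ln 0.62 = 0.687, |log HR| = 0.375, events = 0.33 × 800 = 264. Then √(264/4) × 0.375 − 1.960 ≈ 1.09, power 86.2%.

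**Step 3. Crude against adjusted power by simulation.** 800 patients, overall risks held at 28% and 38%, a hazard that falls over time, censoring at a fixed horizon, two-sided Wald tests, 2,000 runs per setting (Monte Carlo standard error about 0.8 point).

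| Adjusted for (assumed effect) | Crude | Adjusted | Gain (points) |
|---|---|---|---|
| Age above median HR 1.5, non-shockable (15%) HR 2 | 86.2% | 87.9% | 1.7 |
| Same, HR 2 and 3 | 85.0% | 89.2% | 4.2 |
| Same, HR 2.5 and 4 | 87.7% | 94.2% | 6.5 |
| Continuous score, HR per SD 1.65 | 86.7% | 90.1% | 3.4 |
| Continuous score, HR per SD 2.23 | 86.5% | 93.4% | 6.9 |
| Continuous score, HR per SD 2.72 | 87.0% | 96.2% | 9.2 |
| Covariate with no effect | 85.4% | 85.4% | 0 |
| Other factorial allocation only, HR 0.69 | 86.0% | 86.5% | 0.5 |
| Site only, HR 1.3 | 87.3% | 87.8% | 0.5 |

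A still stronger score (HR per SD 3.67) gave 85.5% to 98.9%; I do not rely on it.

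**Step 4. Validity and estimand.** With no treatment effect and a score of HR 2.72 per SD (3,000 runs), the crude test rejected in 4.9% and the adjusted test in 5.0%. In the three score settings of the table the crude hazard ratio averaged about 0.68, close to the design value of 0.687. The adjusted values were 0.67, 0.65 and 0.63.

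**Step 5. Chance imbalance.** A factor with 15% prevalence can differ between arms by about 1.96·√(2·0.15·0.85/400) = 0.05. If its hazard ratio is 3, the crude log hazard ratio shifts by roughly 0.05 × ln 3 ≈ 0.05, about 14% of 0.375.

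**The case against.** The strongest reply is that nothing here is wrong. The crude test holds its type I error, is stated clearly in advance, and matches the unadjusted basis that reproduces the 732. Power at 800 is already above 0.8. This stands: the point is about efficiency and is not an error in the plan.

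Several stronger readings are tempting and fail:
- **That omitting covariates biases the hazard ratio toward 1.** The crude model recovers the planned marginal effect. The adjusted value lies further from 1 because it estimates a conditional hazard ratio.
- **That chance imbalance is a defect.** It is ordinary sampling error, which the confidence interval already covers.
- **That ignoring site and the other allocation wastes power.** Each adds about 0.5 point. In a balanced factorial trial the marginal test loses almost nothing, and the interaction of the two factors is analysed anyway.
- **That the document shows these predictors to be strong.** It gives no hazard ratio, AUC or prevalence for any of them.

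Timing also counts. Recruitment has ended, interim analyses have been done, oxygen allocation is open label, and no further protocol changes are planned. Replacing a primary model at that stage invites questions. This bears on how the change is made and documented, but does not remove the gain. An unseen analysis plan may contain adjusted models; the article nonetheless fixes the primary one as crude.

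**Conclusion.** The point holds as an efficiency improvement. Crude power at 800 patients is about 84-86%. Adjusting for prognostic baseline covariates would add roughly 2 to 9 points, with type I error unchanged.

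The size depends on assumed covariate strength. The lower part of the range comes from weak binary covariates, the top from a strong continuous score, and the gain is nil if the covariates are not prognostic. The simulations used age split at the median or a single score, so they bracket the proposed model and do not reproduce it exactly. The case rests on baseline covariates alone; site and the other allocation are no part of it. A reader should not infer that the crude analysis is invalid or biased.

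**What to change.** Before unblinding, name a short list of baseline covariates in the primary Cox model for each intervention, for example age as a continuous variable and shockable rhythm. Report the crude hazard ratio beside the adjusted one as a supporting analysis.

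Give each covariate one definition. Suspected STEMI, if used, needs this most: the Primary objective ties it to the initial ECG, while section {20b} describes it as the suspected cause of the arrest.

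There was a window for this. Trial status places unblinding and analysis after 90-day follow-up, and Dissemination plans keeps the arms coded until the steering group has agreed on the analysis. Date the change and record that it was made without sight of outcomes by arm. This matters especially for oxygenation, where individual allocations are known to staff.

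The cost is wording and documentation, with no new data. The adjusted hazard ratio is conditional and must be labelled so, and a late change to the primary model has to be explained in the report.

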**Methods:**

Investigator-initiated, dual-center, randomized clinical trial in comatose OHCA patients admitted to an intensive cardiac care unit. Patients are eligible for inclusion if unconscious, older than 18 years of age, and have return of spontaneous circulation for more than 20 min.

Intervention: allocation 1:1:1:1 into a group defined by (a) blood pressure targets in double-blind intervention targeting a mean arterial blood pressure of 63 or 77 mmHg and (b) restrictive (9–10 kPa) or liberal (13–14 kPa) of arterial oxygen concentration during mechanical ventilation. As a subordinate intervention, device-based active fever management is discontinued after 36 h or 72. Patients will otherwise receive protocolized standard of care according to international guidelines, including targeted temperature management at 36 °C for 24 h, sedation with fentanyl and propofol, and multimodal neuro-prognostication. Primary endpoint: Discharge from hospital in poor neurological status (Cerebral Performance category 3 or 4) or death, whichever comes first. Secondary outcomes: Time to initiation of renal replacement therapy or death, neuron-specific enolase (NSE) level at 48 h, MOCA score at day 90, Modified Ranking Scale (mRS) and CPC at 3 months, NT-pro-BNP at 90 days, eGFR and LVEF at 90 days, daily cumulated vasopressor requirement during ICU stay, and need for a combination of vasopressors and inotropic agents or mechanical circulatory support.

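### MoCA, mRS and CPC at 3 months are assigned to a t test with a log step that is undefined at zero and cannot mend a two-peaked distribution, so the comparison mainly re-tests mortality

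*Protocol article*

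**What the plan says.** In the protocol article, Statistical methods for primary and secondary outcomes {20a} puts a mixed list of endpoints under one rule. The list runs "NSE, MOCA score, Modified Rankin scale and Cerebral performance score, NT-pro-BNP, eGFR, and LVEF", followed by daily cumulated vasopressor requirement. All of them go to a t test, and "logarithmic transformation will be applied if data is skewed". The section gives no threshold for skewness and no offset for zeros. It states no ordinal, rank-based or survivor analysis for these endpoints.

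The Secondary objective lists under Objectives {7} and Outcomes {12} say how absent values are filled:
- **MoCA:** "lowest score allocated to patients not available for follow-up, including deceased patients".
- **NT-proBNP:** "highest value allocated to patients not available for follow-up". Deaths are not named.
- **mRS and CPC:** listed only as "Modified Ranking Scale (mRS) and CPC at 3 months". No assignment is stated, but death is a category of both scales.

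Sample size {14} gives the expected share of deaths: "Prior data indicate the 6-month mortality is 33% overall". It also expects fewer than 5% missing follow-up assessments, so most assigned values would come from deaths.

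**The concern.** The article's section on cognitive and neurological outcome says that CPC, mRS and MoCA serve to estimate the interventions' impact on cognitive function. Under the stated rule about a third of patients sit at one extreme value, and the survivors cluster towards the other end. The variance of such a variable comes mostly from who died, so a real shift among survivors is diluted.

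The remedy offered for skewness does not help. It does not exist for a score of zero, and a monotone transformation leaves two peaks as two peaks. At stake is whether three secondary outcomes can add anything to the separate comparison of time to death.

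**Working it through.** The article states no power or effect size for these endpoints, so there is no figure of the plan to reproduce.

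**Inputs from Sample size {14}:** 400 per arm, 33% deaths overall, 28% vs 38% as the design contrast, alpha 0.05. Explanation for the choice of comparators {6b} states two-sided tests.

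**Inputs assumed:** MoCA in survivors has mean 25 and SD 4 with a ceiling of 30, and deaths score 0. Deaths score 6 on mRS and 5 on CPC. Survivor distributions for mRS and CPC are given below. The scale ranges (MoCA 0–30, mRS 0–6, CPC 1–5) are general knowledge of the instruments.

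**1. The log step.** log(0) is minus infinity. This affects mRS 0, and MoCA 0 if the lowest score means the scale minimum. It does not affect CPC or NT-proBNP. With 33% of patients at 0, MoCA is left-skewed (skewness −0.54), and log(x+1) makes it worse (−0.70). A t test on log(x+1) has power of about 5% for a 1.5-point survivor difference.

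**2. Share of MoCA variance due to death.** With m the death share, and μ and σ the survivor mean and SD:

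Var = (1−m)(σ² + μ²) − [(1−m)μ]² = 0.67 × 641 − 16.75² = 429.47 − 280.56 = 148.91, so SD = 12.20.

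Death part = m(1−m)μ² / Var = 0.33 × 0.67 × 625 / 148.91 = 138.19 / 148.91 = 93%. For survivor SD 5 to 3 the share runs from 89% to 96%.

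**3. MoCA power, 1.5-point survivor difference, equal mortality.** Composite mean difference = 0.67 × 1.5 = 1.005. SE = 12.20 × √(2/400) = 0.863. z = 1.165, and power = Φ(1.165 − 1.96) = 0.21. Simulation with the ceiling at 30, which trims the difference, gives about 0.16. The Wilcoxon test with death as worst rank gives about 0.64.

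**4. CPC power.** Assumed probabilities for CPC 1 to 5 are 0.55/0.07/0.04/0.01/0.33 vs 0.45/0.15/0.06/0.01/0.33. Means are 2.50 and 2.62; variances are 3.35 and 3.14. SE = √(6.49/400) = 0.127. z = 0.12/0.127 = 0.94, and power = Φ(−1.02) = 0.15. Simulation gives 0.15 for the t test and 0.38 for Wilcoxon. A smaller assumed shift (survivor means 1.29 vs 1.165) gives 0.10 vs 0.17.

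**5. mRS power.** Assumed survivor probabilities for mRS 0 to 5 are 0.30/0.30/0.17/0.12/0.07/0.04 vs 0.38/0.30/0.15/0.10/0.05/0.02 (means 1.48 and 1.20). Composite means are 2.972 and 2.784; variances are 5.85 and 6.21. SE = √(12.06/400) = 0.174. z = 1.08, and power = 0.19. Simulation gives 0.18 for the t test and 0.24 for Wilcoxon. Another assumed shift gave about 0.19 vs 0.32.

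**6. Mortality effect only (28% vs 38%).** MoCA mean difference = 0.10 × 25 = 2.5. z = 2.5/0.863 = 2.90, and power = Φ(0.94) = 0.83. Simulation gives about 0.84 for the t test and 0.71 for Wilcoxon. The planned MoCA comparison is therefore sensitive to mortality and has little sensitivity to function among survivors.

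**7. NT-proBNP.** Assumed log-normal in survivors (median 500, log-SD 1.2), 22% lower in one arm, and 33% of patients set to the sample maximum. Log t test about 0.24, Wilcoxon about 0.27.

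**The case against.** The strongest defence is that giving death the worst value is a legitimate composite. At 400 per arm the t test on it holds its size, and a mean difference in it is well defined. This stands: the type I error is not at fault, and a reader who infers that the comparison is invalid or cannot be interpreted goes too far. The weakness lies in power and in what the difference reflects.

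It is also true that the log step is conditional on skewness, with no threshold. Under the assumed distributions skewness is moderate (about −0.54 for MoCA, 0.54 for CPC, 0.28 for one mRS distribution), so the log may never be used. If the lowest score means the lowest observed score, MoCA zeros may be few. The two peaks remain in each case.

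A reader might extend the charge to NT-proBNP. The documents do not support that. Its values are positive, the log is defined and is the usual choice, and the stated rule would trigger it for log-normal data. The very low power of an untransformed t test (0.06 under the same assumptions) is therefore not the planned analysis. A rank test gains little over the log t test.

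Lastly, a rank test does not separate death from function either. In the scenarios with survivor means of 1.48 vs 1.20 for mRS and 1.29 vs 1.165 for CPC, a survivors-only t test had power of 66% and 72%, far above either composite test. That comparison conditions on survival, so it suits description rather than testing, but it shows why survivors' values should be reported.

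**Conclusion.** The point holds for MoCA, mRS and CPC. The rule is written in the article, so it is not a detail left to an unseen analysis plan. The log step is undefined at mRS 0, and at MoCA 0 on one reading. The t test mainly repeats the mortality comparison.

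The loss is large for MoCA (about 0.16 vs 0.64 for a 1.5-point survivor difference). It is smaller and depends on the assumed shift for CPC (0.10–0.15 vs 0.17–0.38) and mRS (about 0.18 vs 0.24–0.32). These figures rest on assumed survivor distributions, on equal 33% mortality taken from a 6-month figure, and on the worst category for deaths in mRS and CPC, which the article does not state.

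Only secondary outcomes are affected. The primary outcome and time to death have their own proportional hazards analyses. The change should be made, but the trial's main conclusion does not depend on it.

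**What to change.** - **mRS and CPC:** analyse as ordinal outcomes with death as the worst category, by a proportional-odds model reporting the common odds ratio with its confidence interval.
- **MoCA:** Wilcoxon test with death as worst rank, and a rank-based effect estimate. State whether the lowest score means the scale minimum or the lowest observed score.
- **Survivors:** report their MoCA, mRS and CPC values by arm, descriptively.
- **NSE, NT-proBNP, eGFR, LVEF and vasopressor requirement:** keep the t test, with log if skewed. Nothing here justifies removing it from any of them. Vasopressor values of zero would need a stated rule before any log is taken.
- **NT-proBNP:** a rank test is optional, as a check on dependence on the assigned highest value.

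The cost is plan wording and a few lines of code, with no change to data collection. Trial status places unblinding and analysis after the 90-day follow-up, so the change should be dated before unblinding. The downside is lower MoCA power if mortality alone differs (about 0.71 vs 0.84 at 28% vs 38%). That matters little, because time to death is compared separately.
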